### Aim 1: Adaptation and integration of FFIT and Health*e*Steps™ to create Hockey FIT

Hockey FIT was adapted from FFIT for the Canadian context using the love of hockey to encourage middle-aged, overweight and obese men to lose weight, increase physical activity and live a healthier lifestyle.

The Principal Investigator and other members of the Central Research Team (including the coach for the London site) went to Glasgow, Scotland in January 2015 to meet with FFIT researchers and observe FFIT sessions. While there, research team members attended two 90-min FFIT sessions at different clubs and were introduced to the format used to deliver FFIT programs, and coaching techniques to make the sessions enjoyable and interactive. The FFIT Coach Handbook was used as a reference for creating Hockey FIT sessions and developing the Hockey FIT Coach and Participant Handbooks.

We adopted the study design used by FFIT (see Methods section), but instead of targeting at-risk male soccer fans as was done in Scotland, we focused on hockey fans in Canada. The lifestyle prescription and the technology support tools protocols from the Health*e*Steps™ program [43, 47] were incorporated into the adapted FFIT approach, to develop Hockey FIT. As part of the Health*e*Steps™ program, participants receive individualized healthy living prescriptions for exercise, physical activity (step counts) and healthy eating, and are supported in-person to achieve their prescriptions and set goals with the help of a trained coach. To support longer-term maintenance of healthy lifestyles, participants are also offered free-of-charge access to technology-based coaching and support options (e.g., smartphone apps, private web-based social network, and telephone coaching).

Throughout the design of Hockey FIT, the research team made changes to the FFIT program design, to ensure the content followed Canadian guidelines and would resonate with Canadians. This included changing wording and doing conversions in some of the measurement tools (e.g., chips to fries; converting units of pints to cups; etc.). As well, Canadian resources were substituted in place of their British counterparts (e.g., Canada’s Food Guide [48] and Canadian Physical Activity Guidelines [49]). During FFIT, all sessions took place at the home stadium of the soccer team and were run by club community coaches (i.e., employees of the soccer clubs). For Hockey FIT, sessions were held at either the home arena of the hockey team or at a local fitness club and coaches were University-level students.

The Coach and Participant Handbooks were edited and reviewed by the Hockey FIT coaches, the Principal Investigator and other research team members in development of the final versions. The coaches ran five mock Hockey FIT sessions, using members of the research team and their friends and/or family as study participants. The research team also met weekly during the Hockey FIT program delivery to discuss progress, fidelity and further changes to the program.

### Aim 2: Potential for Hockey FIT to positively impact health outcomes

#### Study design

We conducted a 12-week, two-arm, pilot pRCT of Hockey FIT, as well as a process evaluation of the Hockey FIT program, in which male hockey fans of two OHL teams (London Knights and Sarnia Sting), were individually randomized (1:1) to the Intervention (Hockey FIT) group (starting Hockey FIT program immediately) or the Comparator (Wait-List Control) group (starting Hockey FIT program after a 12-week delay). The 12-week active phase of the Hockey FIT intervention was followed by a 40-week maintenance phase. Measurement sessions were conducted at baseline and 12 weeks (both groups) and then again at 12 months (intervention group only). See Fig. 1 for study flow diagram.

**Fig. 1 Fig1:**
[figure not shown]
Flow Diagram for the Hockey Fans in Training Pilot Pragmatic Randomized Controlled Trial

Study recruitment began in April 2015 and the intervention periods started on May 12, 2015 (London site) and May 27, 2015 (Sarnia site). Western University Health Sciences Research Ethics Board approved this study and all participants provided written informed consent. The pRCT portion of this study was registered on February 26, 2015 with ClinicalTrials.gov (identifier: NCT02396524).

#### Location

The Central Research Team is located at Western University (London, ON, Canada). The London Knights team is in a medium-sized media market in London, Ontario (population 366,151 in 2011), and the Sarnia Sting team is in a smaller urban centre in Sarnia, Ontario (population 89,555 in 2011). The Hockey FIT program sessions were delivered at GoodLife Fitness Centres Inc., Budweiser Gardens (home arena for the London Knights), or the RBC Centre (home arena for the Sarnia Sting). All measurement sessions were conducted at either Western University (London site) or the RBC Centre (Sarnia site).

#### Sample size

A recruitment target of 80 male hockey fans of the London Knights and Sarnia Sting (40 per team; 20 men per arm within each team) was based on a sample size calculation for a subsequent full-scale RCT, following methods by FFIT [15]. To detect a 5 % difference in weight loss between intervention and comparison groups at 12 months, with a standard deviation of 19.9 %, 80 % power and a 0.05 two-sided significance level, 250 men are required in each arm [50]. To allow for 25 % loss to follow-up, a very conservative estimate, the sample size was increased to 335 men in each arm. A target of 670 men reflects the need to recruit 40 male hockey fans from 17 different OHL teams. The need to recruit 40 male hockey fans per site is reflected in this pilot trial.

#### Recruitment & participants

Participants were recruited through a variety of methods: team email blasts, team social media accounts (i.e., team twitter feed posts), posters, traditional media-based advertisements (newspaper, TV, radio, community magazines), Hockey FIT website [51], word of mouth, and/or direct contact with potential recruits at the OHL team arena on game day. Those interested in participating in the study contacted the Hockey FIT Research Coordinator by email or telephone. The Research Coordinator pre-screened individuals for eligibility by phone or email; specifically, interested individuals were asked about their gender, age, height, weight and availability to attend Hockey FIT sessions on a certain day of the week, for 12 weeks, starting on a set date. Individuals deemed likely to be eligible were then invited to attend an in-person screening session. *Inclusion criteria:* Men aged 35–65 years, with an objectively measured BMI of at least 28 kg/m^2^, and meet safety requirements using the Physical Activity Readiness Questionnaire (PAR-Q) [52]. *Exclusion criteria:* Unable to comprehend the letter of information and consent documentation.

#### Screening

The formal screening process for each man lasted approximately 20 min. Screening only proceeded once participants provided written informed consent to participate in the study. Following this, men self-completed the PAR-Q; if a participant answered, “yes” to one or more of seven questions on the PAR-Q, a research team member completed a Health Care Provider Clearance form to highlight specific concerns regarding the man’s ability to perform physical activity. This form was then provided to the Study Physician and Principal Investigator who determined whether the individual was cleared to participate in Hockey FIT. To conclude the screening session, participants were taken individually to a private area for measurements of height (Seca 213 portable stadiometer) and weight (Tanita HD351 digital weight scale). All eligible men were then invited to continue with a baseline measurement session.

#### Randomization, allocation & blinding

Following baseline measurement (including seven days of tracking steps via a pedometer), participants returned for an enrolment and allocation session. The randomization sequence was computer-generated [1:1 in block sizes of 4 and stratified by site (London or Sarnia), using SAS version 9.4 (SAS Statistical Analysis Software)] and concealed using opaque envelopes until interventions were assigned (by an individual not involved in generating the randomization sequence). Participants were allocated in correspondence to the numerical order of the randomization envelopes and their order of appointments.

All participants (intervention and comparator) were provided with copies of Canada’s Food Guide [48] and the Canadian Physical Activity Guidelines [49]. All participants were also given an adverse events log and the research team member allocating participants stressed the importance of keeping the research team and/or their Hockey FIT coach informed of any injuries, illnesses, or changes in medication for the entirety of the study. Participants allocated to the intervention group were informed to keep their pedometer for use over the duration of the program. Participants allocated to the comparator group were asked to return their pedometer and continue with usual activities, without further intervention from the research team. Following completion of the 12-week measurement sessions, participants in the comparator group were invited to take part in the Hockey FIT program, following the exact same protocol as the intervention group.

Due to the nature of the study, participants and coaches could not be blinded to group allocation. During 12-week measurement sessions, a blinded assessor conducted all weight measurements in a separate room; no other measurements were blinded.

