#### Hockey FIT program

##### 12-week active phase

The Hockey FIT program uses group-based delivery to help men achieve changes in health behaviours and indicators. The program was delivered by two trained Hockey FIT coaches (one Head Coach and one Assistant Coach) to groups of 20 men, over 12, weekly, 90-min sessions. See Table 1 for an overview of the 12-week program.

**Table 1 Tab1:** Overview of the Hockey fans in training program (12-week active phase)

Classroom education component	Exercise component
Week 1: Introduction to Hockey FIT & Physical Activity Prescription	
70 min: • Introductions, program overview, ground rules • Discuss eating habits, exercise and activity levels • Introduction to lifestyle prescriptions (Rx), goal-setting, and tracking • Set Physical Activity Rx	20 min: • Group walk
Week 2: Healthy Eating Overview & Healthy Eating Prescription	
65 min: • Review healthy living goals and tracking forms • Set new Physical Activity Rx • Food groups & eating a healthy diet • Formal introduction to SMART goal setting • Set Healthy Eating Rx	25 min: • Group walk
Week 3: Meal Planning & Weight Loss	
60 min: • Review healthy living goals • Set new Physical Activity Rx • Avoiding compensation/trade-off behaviour • Healthy eating planning • Health benefits of losing weight • Calculating 5–10 % weight loss • Importance of support from others	30 min: • Introduction to principles of fitness (10 min) • Warm up exercises (8 min) • Flexibility exercises (2 min) • Walk (10 min)
Week 4: Becoming Fit & Exercise Prescription	
65 min: • Review healthy living goals • Set new Physical Activity Rx • Health benefits of exercise • Overcoming barriers to exercise • Heart rate and Rating of Perceived Exertion • Simple fitness test (STEP test) • Local amenities • Set Exercise Rx	25 min: • Warm up (5 min) • Aerobic exercise (15 min) • Cool down (5 min)
Week 5: Alcohol & Weight Gain	
50 min: • Review healthy living goals • Set new Physical Activity Rx • Alcohol and weight gain • Alcohol units • Planning your drinking • Cutting down on sugary drinks	40 min: • Warm up (5 min) • Aerobic exercise (30 min) • Cool down (5 min)
Week 6: Stages of Change	

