##### 12-week non-completer telephone interviews

Non-completers were defined as participants randomized to the intervention group who attended less than six program sessions (<50 %) and did not attend any of the final six program sessions.

Non-completers were contacted after all 12 sessions were completed and were asked to complete a program exit survey over the phone. Participants were asked about why they initially joined the program, why they stopped attending the program, if their involvement in the program has changed their lifestyle habits, and if (and how) the program could be changed to encourage them to complete the program.

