##### Weekly attendance records

Hockey FIT coaches took attendance at the beginning of each of the 12 weekly sessions for both sites.

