##### Fidelity (Program observations and post session coach reflections)

A member of the Hockey FIT research team was trained to observe program delivery at both London and Sarnia sites. All 12 weekly sessions at both sites were observed and notes were taken during the sessions. These notes detailed the overall session flow (completion of key tasks, classroom setup, interaction among participants, timing, style and method of delivery, and key lessons learned) and were summarized by the central research team. The research team member who observed the program delivery interviewed coaches after each session. Questions were specific to the experience delivering the program components and were standardized to what went well with delivery and what could be done differently.

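### Opportunities to report adverse events before week 12 differ by arm, so any harms table by arm is open to unequal ascertainment

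*Protocol article*

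**What the plan says.** All of this is in the protocol article.

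- **Reporting tool and route** (Randomization, allocation & blinding). Each man receives a log for adverse events at allocation, and staff put weight on "keeping the research team and/or their Hockey FIT coach informed of any injuries, illnesses, or changes in medication for the entirety of the study". The log and the instruction are the same in both arms, and the participant makes the report.
- **Comparator arm before week 12** (same section). These men return the pedometer and are asked to "continue with usual activities, without further intervention from the research team". They are invited into the program only after the 12-week measurements.
- **Intervention arm before week 12** (12-week active phase). Two coaches deliver the program "over 12, weekly, 90-min sessions". Under Weekly attendance records, "Hockey FIT coaches took attendance at the beginning of each of the 12 weekly sessions for both sites". Under Fidelity, "All 12 weekly sessions at both sites were observed and notes were taken during the sessions" by a research team member, who also interviewed the coaches after each session.
- **Men who stop attending** (12-week non-completer telephone interviews). "Non-completers were contacted after all 12 sessions were completed" for an exit survey, which concerns the intervention arm only.
- **Contact common to both arms** (Study design; Outcome evaluation). Both groups have a 12-week measurement session. Every randomized man is contacted at each follow-up, and questionnaires are mailed to those who agree to assessment but cannot or will not attend.
- **Outcome list** (Outcome measures and Table 2). No adverse-event or medication item is listed. Medications are recorded at baseline.

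**The concern.** With participant-initiated reporting, the chance that an event is recorded depends partly on how often the man meets someone to tell. One of the two named recipients, the coach, exists before week 12 only for intervention men. The other, the research team, is present at their weekly sessions through the observer. A comparator man with a strained back has the log and can contact the team, but the article describes no occasion between allocation and week 12 that would prompt him.

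The first 12 weeks are the only randomized comparison, because comparator men then join the program and are not measured again. The program is one of progressive exercise for overweight or obese men, entered after a physical-activity readiness screen with physician review where needed, so injury is a foreseeable harm. If events are ever tabulated by arm, a difference could reflect frequency of contact and not the program. The pilot is meant to inform a full-scale trial, which could inherit the same reporting route.

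**Working it through.** The article states no adverse-event rate and no reporting rate, so there is no figure to reproduce. The check is a comparison of the text by arm, followed by an illustration on assumed values.

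**Step 1: reporting opportunities from allocation to week 12**

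| | Intervention | Comparator |
|---|---|---|
| Adverse events log | yes | yes |
| Instruction to report | yes | yes |
| Coach available as recipient | yes, two | none until after the 12-week measurements |
| Research team member present | observer at every session | none described |
| Weekly occasions | up to 12 | 0 described |
| Exit call for men who left | yes, after the last session | not applicable |
| 12-week measurement session | yes | yes |

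The tool and the instruction are symmetric, and so is the 12-week session. The interim occasions are not.

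**Step 2: effect of unequal capture**

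Inputs: 40 men per arm (Sample size: 20 per arm in each of two teams). Assumed: the same true 12-week risk *p* in both arms, with capture probability *c*I in the intervention arm and *c*C in the comparator arm.

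- Recorded risk = *p* × *c*
- Spurious risk ratio = (*p* × *c*I) / (*p* × *c*C) = *c*I / *c*C, whatever the value of *p*
- Expected recorded count = 40 × *p* × *c*

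With *c*I = 0.90 and *p* = 0.20, the intervention count is 40 × 0.20 × 0.90 = 7.2. For the comparator arm:

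| *c*C | Comparator count | Spurious risk ratio |
|---|---|---|
| 0.90 | 40 × 0.20 × 0.90 = 7.2 | 0.90/0.90 = 1.00 |
| 0.80 | 40 × 0.20 × 0.80 = 6.4 | 0.90/0.80 = 1.13 |
| 0.70 | 40 × 0.20 × 0.70 = 5.6 | 0.90/0.70 = 1.29 |
| 0.60 | 40 × 0.20 × 0.60 = 4.8 | 0.90/0.60 = 1.50 |
| 0.50 | 40 × 0.20 × 0.50 = 4.0 | 0.90/0.50 = 1.80 |

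**Step 3: direction**

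More frequent contact should raise capture in the intervention arm, so a ratio above 1 is the likelier error. One force works the other way: men who leave the program lose the weekly occasions, which lowers *c*I. The ratio would fall below 1 only if *c*I dropped below *c*C. The text makes this less likely but does not exclude it.

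**The case against.** The strongest reply is that the article is a condensed account. It does not say that the log goes uncollected or that no adverse-event question is asked at 12 weeks, and such details commonly sit in a full protocol. The outcome list is not an inventory of everything collected: medications are taken at baseline without appearing in it. What the article does state includes a log common to both arms, the research team as a recipient open to both, a planned 12-week session for both, and contact with all randomized men at each follow-up, including men who left the program. No between-arm comparison of harms is announced.

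Much of this stands. A reader might infer that the log is never retrieved, that comparator men have no planned contact at all, or that harms in the two arms cannot be compared. The documents support none of these. Silence on collection does not show that it was omitted. The 12-week session is a planned contact in both arms. A log that is fully kept and collected in both arms could give equal capture, which is the 1.00 row of the table.

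The objection does not remove the stated route. The article says who reports and to whom, and on that account one arm has weekly access to both recipients while the other has no described interim contact. Any table by arm would carry that asymmetry, even though none is announced yet.

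**Conclusion.** The point holds as a risk of differential ascertainment. Between allocation and week 12 the opportunities to report differ by arm, at up to 12 weekly sessions against no described interim contact. A tabulation of injuries, illnesses or medication changes by arm would most likely lean towards more recorded events in the intervention arm.

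The size is unknown. A spurious risk ratio of 1.8 to 1.0 rests on equal true risk, 90 % capture in the intervention arm and 50 to 90 % in the comparator arm. All of these are assumptions, and the documents do not favour any one row. It would go too far to say that the counts do exaggerate harm, since neither the capture rates nor the net direction can be established from the text. The point does not touch the weight analysis or any other listed outcome. It is worth acting on because the remedy is cheap.

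**What to change.** At the 12-week measurement, and in the mailed questionnaires for men who do not attend, collect the log and put one identical question to every randomized man: any injury, illness or medication change since allocation. Use only that source for any between-arm table, giving number, percentage and 95 % confidence interval. List events volunteered to coaches separately, as a description of the intervention arm.

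If the 12-week sessions are already complete, tabulate events by source, state the ascertainment limit beside the table, and carry the common question into the full-scale trial. If the full protocol already provides for this, a sentence saying so is enough.

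The cost is one item in an existing session and questionnaire pack, with no new visit. The downside is that recall over 12 weeks is less complete than weekly reporting, so the comparable count may miss events that coaches heard about. The separate listing keeps those events in view.

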#### Hockey FIT program

##### 12-week active phase

The Hockey FIT program uses group-based delivery to help men achieve changes in health behaviours and indicators. The program was delivered by two trained Hockey FIT coaches (one Head Coach and one Assistant Coach) to groups of 20 men, over 12, weekly, 90-min sessions. See Table 1 for an overview of the 12-week program.

**Table 1 Tab1:** Overview of the Hockey fans in training program (12-week active phase)

Classroom education component	Exercise component
Week 1: Introduction to Hockey FIT & Physical Activity Prescription	
70 min: • Introductions, program overview, ground rules • Discuss eating habits, exercise and activity levels • Introduction to lifestyle prescriptions (Rx), goal-setting, and tracking • Set Physical Activity Rx	20 min: • Group walk
Week 2: Healthy Eating Overview & Healthy Eating Prescription	
65 min: • Review healthy living goals and tracking forms • Set new Physical Activity Rx • Food groups & eating a healthy diet • Formal introduction to SMART goal setting • Set Healthy Eating Rx	25 min: • Group walk
Week 3: Meal Planning & Weight Loss	
60 min: • Review healthy living goals • Set new Physical Activity Rx • Avoiding compensation/trade-off behaviour • Healthy eating planning • Health benefits of losing weight • Calculating 5–10 % weight loss • Importance of support from others	30 min: • Introduction to principles of fitness (10 min) • Warm up exercises (8 min) • Flexibility exercises (2 min) • Walk (10 min)
Week 4: Becoming Fit & Exercise Prescription	
65 min: • Review healthy living goals • Set new Physical Activity Rx • Health benefits of exercise • Overcoming barriers to exercise • Heart rate and Rating of Perceived Exertion • Simple fitness test (STEP test) • Local amenities • Set Exercise Rx	25 min: • Warm up (5 min) • Aerobic exercise (15 min) • Cool down (5 min)
Week 5: Alcohol & Weight Gain	
50 min: • Review healthy living goals • Set new Physical Activity Rx • Alcohol and weight gain • Alcohol units • Planning your drinking • Cutting down on sugary drinks	40 min: • Warm up (5 min) • Aerobic exercise (30 min) • Cool down (5 min)
Week 6: Stages of Change	
45 min: • Review healthy living goals • Set new Physical Activity Rx • Stages of change • Setbacks and strategies for dealing with them • Shared experiences • Weight taken (to review progress at Week 7)	45 min: • Warm up (5 min) • Strength/muscular endurance exercise (with principles of strength training using body weight) (35 min) • Cool down (5 min)
Week 7: Weight Loss	
45 min: • Review healthy living goals • Set new Physical Activity Rx • Understanding food labels and healthier foods • Hints for better eating including eating breakfast	45 min: • Warm up (5 min) • Strength/muscular endurance exercise (15 min) • Aerobic exercise (15 min) • Cool down (5 min) • Flexibility exercises (5 min)
Week 9: Eating Out	
45 min: • Review healthy living goals • Set new Physical Activity Rx • Making favourite meals healthier • Eating out sensibly • Nutrition in common fast foods & suggestions for making takeout meals ‘less’ unhealthy	45 min: • Warm up (5 min) • Strength/muscular endurance exercise (15 min) • Aerobic exercise (15 min) • Cool down (5 min) • Flexibility exercises (5 min)
Week 10: Avoiding Setbacks & New Exercise Prescription	
55 min: • Review healthy living goals • Set new Physical Activity Rx • Exploring myths about healthy living • Triggers for setbacks and how to avoid them • Re-do simple fitness test (Step Test) & set new Exercise Rx	35 min: • Warm up (5 min) • Strength/muscular endurance exercise (10 min) • Aerobic exercise (10 min) • Cool down (5 min) • Flexibility exercises (5 min)
Week 11: Energy Balance & New Healthy Eating Prescription	
45 min: • Review healthy living goals • Set new Physical Activity Rx • Planning your eating • The energy balance • Locus of control revisited • Set new Healthy Eating Rx	45 min: • Warm up (5 min) • Strength/muscular endurance exercise (25 min) • Cool down (5 min) • Flexibility exercises (10 min)
Week 12: Celebrating Achievements & Next Steps	
60 min: • Celebrating achievement! • Review healthy living goals & set new Rx if necessary (Physical Activity, Healthy Eating & Exercise) • Next steps – includes introduction to suite of eHealth technology support options • Program feedback • Wrap-up	30 min: • Warm up (5 min) • Strength/muscular endurance exercise (20 min) • Cool down (5 min)

All participants received Hockey FIT handbooks at the first session. Nine sessions took place at a local GoodLife Fitness club, whereas three sessions (#1, #5, #11) were held at the affiliated hockey team’s arena. It was not possible to hold all Hockey FIT sessions at the hockey team arena due to logistical reasons; however, sessions at the arenas were critical in that they provided an association between the team and program. Hockey FIT head coaches were male graduate students in Kinesiology with extensive backgrounds in coaching (one with extensive background in hockey coaching). The Hockey FIT assistant coaches were senior female university students in Kinesiology, who also had a background in playing hockey.

Sessions are comprised of: 1) classroom-based education focusing on healthy eating and physical activity, delivered in an interactive, non-didactic style; and 2) exercise sessions where men receive training in aerobic, strength and flexibility exercises, incorporating their love of hockey “off the ice” (i.e., stick handling drills with rubber pucks), and tailored to individual abilities. At the start of the program, more time is allocated to education during each session, but as the program progresses, the amount of time spent on the classroom education decreases, while the amount of time spent on group-based exercise increases. This also coincides with the intensity of the exercise sessions increasing and the educational content becoming more focused on reviewing previously learned content.

Similar to FFIT [6], the delivery of Hockey FIT, but not its core components, is flexible to: 1) allow coaches to run the program to complement their own strengths/weaknesses; 2) match the personalities of a particular group of men; and 3) work within given delivery environments (e.g., arenas, health club facilities, or community centres). Hockey FIT includes components designed to appeal to male hockey fans such as: team-based incentives (i.e., visits from players); elements of competition (i.e., during exercise sessions); and use of humour to help men address sensitive topics (i.e., weight gain).

Coaches also provide instruction on behaviour change techniques (BCTs) effective in physical activity and dietary interventions (e.g., self-monitoring, specific goal setting and review, and feedback on behaviour) [53]. These BCTs are associated with control theory [54] and were mapped to FFIT [6]; the program also draws on other BCTs including social cognitive theory and self-regulation [55]. Coaches promote peer and other forms of social support as these have been shown effective in preventing relapse [53].

At two different time points (session #4 and #10), participants completed the Step Test and Exercise Prescription (STEP) tool in order to receive a personalized target heart rate (65–85 % of estimated maximum heart rate) [41, 44]. Coaches then encouraged participants during aerobic activities to exercise at their training heart rate and/or at a rating of 5–8 on the 10-point modified Borg Rating of Perceived Exertion scale [56]. Throughout the 12 weeks, participants took part in an incremental pedometer-based walking program. Participants also set and tracked individualized lifestyle prescriptions for physical activity (steps), exercise and healthy eating; these prescriptions were modified over the 12-week program when necessary to match participant progress.

In preparing for the *Maintenance Phase*, men were introduced to eHealth technology support tools, including the Health*e*Steps smartphone app (providing a virtual coach and tools to sustain increased physical activity) and their own team’s Hockey FIT social network – a secure, closed, web-based network of their Hockey FIT group and Head Coach on Tyze Personal Networks (i.e., participants could not invite other individuals into the network).

